### Interventions and Comparators

#### Intervention

The simulator will be first administered at the March training weekends for each year. We will use these training weekends to test participants at baseline on the simulator and collect demographic data via survey. The simulator will be set up as one of the 15-minute assessment stations in the training weekend. Simulator sets will be distributed to individual trainees following the training weekend. Upon delivery of the simulator sets, the principal investigator will also provide aid to the trainee in identifying an appropriate environment for the simulator and address any setup issues.

It is then expected that trainees will undertake, at minimum, monthly 15-minute practices on the simulator for the next 6 months of training. These practice data are sent to a cloud server after each use. Note that the simulator training will be in addition to any routine training they will receive at their respective hospitals. Over this time, primary end points for each in-theater case will be taken over the course of follow-up through District Health Board (DHB) records, including patient picture archiving and communication system (PACS) records and trainees’ logbooks.

We will request intervention trainees to write out relevant patient data and end point results as the cases present to maximize accuracy. Trainees will be reminded monthly by email to provide case data and practice on the simulator. Their simulator performance will be assessed again in a controlled environment during the November training weekend. At this point, secondary end points will also be collected via survey.

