### Statistical Analysis

Operative outcomes using data taken before or without ongoing exposure to the simulator will be compared to outcomes using data from trainees who have used the simulator after 1 year. Comparisons will be performed using Student *t* tests or Wilcoxon Rank Sum tests (depending on the distribution of the data) for theater time and chi-square or Fischer exact tests (depending on the count of the outcome) for the number of complications, number of accurate pin placements, and number of mistakes.

Primary end points will be plotted on separate cumulative sum curves to show trends in performance over the course of follow-up by individuals and aggregated according to pre- and post–1-year simulator training. Control limits will be determined based on values identified in the literature and consultation with senior orthopedic consultants [22-24].

Accuracy of pin placements in subsets of images measured twice must be based on anterior-posterior, lateral, and oblique radiographs. Measurements taken will need to be compared for intra- and interobserver reliability using Bland-Altman plots and intraclass correlation scores.

The results from the familiarity questionnaire will be summarized as responses per category.

Univariable ordinary least squares regression analyses will be used to examine the association of theater time, number of complications (including nonideal unions), and number of x-ray shoots with independent variables. Logistic regression will be used to examine the association of accurate pin placement (yes or no) with independent variables. Independent variables will be the number of times the simulator is used, the number of SCHF procedures performed prior to intervention, Gartland classification, scores on tests of spatial awareness, and the number of SCHF procedures performed during the intervention. Independent variables that are significantly associated with a primary end point (*P*<.05) will be included as covariates in multivariable analyses. Appropriate model diagnostics, and where required, data transformations will be used.

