## Discussion

### Strengths and Limitations

This study is not a randomized trial and uses historical comparators, which may limit our ability to generalize the results due to confounding factors. We aim to mitigate the effects of potential confounding factors by matching comparators based on training experience. Potential confounding variables will be collected at baseline for both groups and explored for associations with our outcome measures. In monitoring the learning curves of both groups over time, a difference-in-difference analysis will be performed to explore simulator effects. The quality of patient data and logbook entries by historical trainees will determine the quality of our comparator data; however, we are confident that the primary outcomes we have chosen are sufficiently routinely collected for surgical cases.

This is the first surgical simulator validation study conducted across all New Zealand centers with early-stage trainees and will be invaluable for establishing a pathway for future New Zealand studies. In collaborating with the training organization at the early stages of testing, and continuous collaboration over the course of the project, the formal integration of this simulator into training can be streamlined. Collaborations for this study also exist with orthopedic surgeons in the United States. Successful multicenter testing in New Zealand is likely to lead to further testing in the United States, thereby improving the external validity of this simulator and possible integration into international training programs. 

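### The regression on number of simulator uses omits the March baseline simulator result, so starting skill may confound the use slope

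*Protocol article*

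**What the plan says.** The Intervention section says of the March weekends: "We will use these training weekends to test participants at baseline on the simulator and collect demographic data via survey". Simulator sets are handed out only afterwards, so this result precedes home practice. Practice is then set as a floor without a ceiling: "It is then expected that trainees will undertake, at minimum, monthly 15-minute practices on the simulator for the next 6 months of training". At the end of follow-up, "Their simulator performance will be assessed again in a controlled environment during the November training weekend".

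The Statistical Analysis section uses ordinary least squares for theater time, complications and x-ray shots. For pin accuracy, "Logistic regression will be used to examine the association of accurate pin placement (yes or no) with independent variables". The predictors are given as a complete list: "Independent variables will be the number of times the simulator is used, the number of SCHF procedures performed prior to intervention, Gartland classification", then "scores on tests of spatial awareness, and the number of SCHF procedures performed during the intervention". Those with univariable P<.05 "will be included as covariates in multivariable analyses". The March simulator result is not on the list.

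Strengths and Limitations adds: "Potential confounding variables will be collected at baseline for both groups and explored for associations with our outcome measures".

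**The concern.** The number of simulator uses is an exposure that trainees partly choose. A trainee who starts badly may practise more to catch up, or an able and keen one may practise more from interest. In either case the slope of theater time, x-ray shots or pin accuracy on use carries some of the trainee's starting ability. If weaker starters practise more, the benefit of practice is understated. If abler starters practise more, it is overstated.

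The March result is the one direct measure of pinning performance taken before practice begins. It is already collected on the trainees concerned, but the stated predictor list does not use it. At stake is how the plan's regression on amount of use can be read, and that regression bears on whether simulator skill transfers to theater.

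**Working it through.** **Inputs from the protocol (Recruitment).** There are 41 comparators, a target of 14 intervention trainees in 2022, 10 to 15 new trainees a year (12 on average), and a total of about 65. The total reproduces: 41 + 2 × 12 = 65, and also 41 + 14 + 10 = 65. The intervention cohort is therefore about 24 (2 × 12, or 14 + 10) to 29 (14 + 15). The 65 is a feasibility count. No effect size, SD, correlation or power is stated.

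**Assumptions.** All variables are standardised, with one observation per trainee. *g* is the partial effect of the March score on the outcome, and *r* is the correlation between March score and number of uses. The documents give neither, so ranges are shown.

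**Bias.** The omitted-variable formula is bias in the use slope = *g* × *r*. It is zero if either term is zero. Example with theater time, where lower is better: true slope −0.30 and skill effect −0.5.
- *r* = −0.3: −0.30 + (−0.5)(−0.3) = −0.15, so half the effect is hidden.
- *r* = +0.3: −0.30 + (−0.5)(0.3) = −0.45, so the effect is inflated by half.

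**Standard error and false positives when the true use slope is 0, n = 24.**
- SE unadjusted = √[(1 − (*gr*)²)/(n − 2)]
- SE adjusted = √[(1 − *g*²)/((n − 3)(1 − *r*²))]
- The rejection rate of the unadjusted two-sided 5% test comes from the noncentral t.

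| *g* | abs. *r* | abs. bias (SD) | Unadjusted rejection | SE adjusted / unadjusted |
|---|---|---|---|---|
| 0.5 | 0 | 0 | 5.0% | 0.189/0.213 = 0.89 |
| 0.3 | 0.3 | 0.09 | 6.9% | 0.218/0.212 = 1.03 |
| 0.5 | 0.3 | 0.15 | 10.5% | 0.198/0.211 = 0.94 |
| 0.5 | 0.5 | 0.25 | 21.2% | 0.218/0.206 = 1.06 |
| 0 | 0.5 | 0 | 5.0% | 0.252/0.213 = 1.18 |

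At n = 29 the three rows with bias give rejection rates of 7.4%, 11.8% and 25.3%, with similar SE ratios.

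**Power.** Take n = 24, a use-outcome correlation of 0.4 and a noncentrality of 0.4/√(1 − 0.16) × √24 = 2.14. Unadjusted power is 53.4%. Adjusting for a score with outcome correlation 0.5 multiplies the noncentrality by √(1 − *r*²)/√(1 − 0.25) and leaves 21 degrees of freedom:
- *r* = 0: 65.4%
- *r* = 0.3: 61.3%
- *r* = 0.5: 53.2%

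If the score-outcome correlation is only 0.3, power is 53.2% at *r* = 0.3 and 45.7% at *r* = 0.5. A gain of 12 points therefore needs *r* = 0, the case in which there is no bias to remove.

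**The P<.05 screen.** By Fisher's z with n = 24, the chance that a covariate passes is about Φ(atanh(ρ)√21 − 1.96). That is 29% at ρ = 0.3 and 71% at ρ = 0.5. Adding the March score only as a further candidate would often lose it, and the existing proxies face the same risk.

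**The case against.** Much of the case on the other side stands.

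- **Starting level is not ignored.** Prior SCHF procedures and spatial awareness scores are on the list. They would absorb some of the confounding, so the bias figures above, which treat skill as wholly uncontrolled, are not forecasts. But one measures case exposure and the other general aptitude, and either may fail the screen.
- **A general look at confounders is promised.** That sentence concerns variables collected in both groups. No simulator test is described for comparators, so the March result falls outside it as worded, and exploring associations is not the same as adjusting.
- **The list may have a reason.** The protocol does not restrict the regression to intervention trainees. If comparators enter with zero uses, the score is absent for 41 of about 65. The remedy therefore means a model fitted within one cohort, not one more term in a pooled model.
- **The calculation is simpler than the data.** End points are collected per case. Several cases per trainee would change the standard errors, though not the bias formula. In the logistic model for pin accuracy, adjustment does not generally shrink the coefficient's standard error.

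A reader might go further than the documents allow in three ways. One is to infer that the slope *is* biased and precision *is* lost. Neither is shown, because the correlations are unknown and adjustment can widen the standard error. Another is that the simulator scores serve only for a learning curve. In fact simulator mistakes and simulator pinning accuracy are secondary end points, and the number of mistakes is tested. The last is that the study's main conclusion is undermined. The objective rests on intervention versus comparator trainees, where this score plays no part.

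**Conclusion.** The point holds as a risk of confounding in one analysis. Practice above the minimum is self-selected, and a pre-practice measure of the relevant skill is collected but missing from a predictor list stated as complete. The listed proxies cover starting skill only in part and may be screened out.

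The size cannot be fixed from the documents. Under assumed skill effects of 0.3 to 0.5 and use-skill correlations of 0.3 to 0.5 in absolute value, the slope shifts by 0.09 to 0.25 SD. A nominal 5% test of a true zero slope then rejects about 7% to 21% of the time with 24 trainees, and 7% to 25% with 29. With either quantity at zero there is no bias, and the direction is unknown.

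The argument for adjustment is confounding, not precision. This is a modest, inexpensive improvement to an association analysis in a pilot study.

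**What to change.** In Statistical Analysis:

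1. State that the models for number of simulator uses are fitted within the intervention cohort.
2. Name one March simulator measure in advance, for example simulator pinning accuracy, which is already defined among the secondary end points. Include it as a fixed covariate in those models, exempt from the P<.05 screen.
3. Adjust any analysis of the November simulator result for the March result in the same way.
4. Leave the between-cohort comparison as it is, because comparators have no simulator score.

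No extra testing is needed, provided the chosen measure is recorded at the March station. The cost is a separately specified within-cohort model, one degree of freedom among about 24 to 29 trainees, and possibly a wider standard error: 3% to 18% wider in the unfavourable settings tabulated, where the score is weakly prognostic or correlated with use. No gain in precision should be promised, least of all for the logistic model. Choosing the measure before the outcome data are analysed avoids a post hoc choice of covariate.

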#### Patient Data

Data such as the National Health Index (NHI) number and surgical details will be collected from trainee logbooks. The following data will be collected from the corresponding DHB records: NHI number; time and date of presentation to the emergency department; age; sex; ethnicity; side of fracture; Gartland classification of fractures—type I, type II, type III, and type IV; the presence of consultant or any other assistants in surgery.

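### Covariates enter the multivariable models only at univariable P<.05, a screen applied even to simulator use, while consultant presence and patient age are collected but are not candidates

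*Protocol article*

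**What the plan says.** All references are to the protocol article.

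- **Candidate list (Statistical Analysis).** "Independent variables will be the number of times the simulator is used, the number of SCHF procedures performed prior to intervention, Gartland classification", followed by "scores on tests of spatial awareness, and the number of SCHF procedures performed during the intervention". That makes five variables.
- **Entry rule (same section).** "Independent variables that are significantly associated with a primary end point", with the threshold P<.05, "will be included as covariates in multivariable analyses".
- **Group comparison (same section).** "Comparisons will be performed using Student *t* tests or Wilcoxon Rank Sum tests" for theater time, and chi-square or exact tests for counts. None of these is adjusted.
- **Data collected (Patient Data).** The per-case items include patient age, Gartland class and "the presence of consultant or any other assistants in surgery". Of these three, only Gartland class is a candidate.
- **Design (Recruitment; Strengths and Limitations).** "This study is not a randomized trial and uses historical comparators". Matching is on time in registered training only. On confounding the article adds: "Potential confounding variables will be collected at baseline for both groups and explored for associations with our outcome measures". It also promises a difference-in-difference analysis of the learning curves.

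**The concern.** A confounder matters because it differs between the cohorts and also affects the outcome. A univariable test against the outcome ignores the first link, and with few trainees it has little power for the second. Non-significance then removes a variable whether or not it is harmless.

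The article itself gives reasons why the cohorts might differ. They come from different calendar years, intervention follow-up runs May to November while comparator follow-up starts in February, and the rotation schedule changed at the end of 2020. Who else is in theater could plausibly bear on theater time, fluoroscopy shots and pin accuracy, yet that variable cannot enter the model under the stated rule.

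The screen also covers the number of simulator uses, and the list contains no separate cohort term. Read literally, the multivariable model for an end point may contain no term for the intervention at all. What is at stake is whether the adjusted analysis estimates a simulator effect, and whether it offsets the weakness of the historical comparison.

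**Working it through.** **1. The plan's own figure.** Recruitment gives 41 comparators and an average of 12 new trainees a year. Two intervention years give 41 + 2 × 12 = 65, which matches the stated approximate total. Using the 14 trainees planned for 2022 gives 41 + 14 + 12 = 67, also compatible with it.

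**2. Chance that a trainee-level variable passes the screen.** For true correlation r with the outcome, one value per trainee and a two-sided 5% test, the Fisher z approximation is

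P(pass) = Φ(atanh(r)·√(n−3) − 1.96) + Φ(−atanh(r)·√(n−3) − 1.96).

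With n = 65, √62 = 7.874. For r = 0.20, atanh(r) = 0.2027 and 0.2027 × 7.874 = 1.596, so P(pass) ≈ Φ(−0.364) = 0.358. For r = 0.25, 0.2554 × 7.874 = 2.011, so P(pass) ≈ Φ(0.051) = 0.520.

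| r | passes | dropped |
|---|---|---|
| 0.15 | 22% | 78% |
| 0.20 | 36% | 64% |
| 0.25 | 52% | 48% |
| 0.30 | 68% | 32% |
| 0.40 | 92% | 8% |

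The correlations are assumptions, since the article gives none. The same arithmetic applies to simulator use if it is analysed as one value per trainee with comparators coded zero. If that regression uses only the roughly 24 intervention trainees, r = 0.20 passes 15% of the time and r = 0.25 passes 22%.

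**3. Effect on a cohort contrast.** The setup was 41 versus 24 trainees, one outcome value each, no true simulator effect and a binary confounder, with 10,000 runs per row. Confounder strength and prevalence are assumed. The cohort term was always in the model, which the article does not specify.

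| Effect (SD) | Prevalence, comparator / intervention | Dropped by screen | Bias (SD): never adjusted | Bias (SD): screened | Bias (SD): forced in | False positives: never / screened / forced |
|---|---|---|---|---|---|---|
| 0.3 | 40% / 60% | 78.1% | 0.061 | 0.034 | 0.002 | 5.7% / 5.1% / 5.0% |
| 0.3 | 30% / 70% | 78.0% | 0.121 | 0.067 | 0.003 | 6.9% / 5.1% / 5.0% |
| 0.5 | 40% / 60% | 49.7% | 0.104 | 0.033 | 0.002 | 7.1% / 5.2% / 5.1% |
| 0.5 | 30% / 70% | 49.6% | 0.196 | 0.056 | −0.004 | 11.1% / 5.2% / 4.7% |
| 0.8 | 40% / 60% | 11.4% | 0.163 | 0.010 | 0.001 | 8.9% / 5.2% / 5.1% |
| 0.8 | 30% / 70% | 12.0% | 0.319 | 0.019 | 0.000 | 21.1% / 5.2% / 4.8% |

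The never-adjusted column agrees with the direct formula, effect × prevalence difference; for example 0.5 × (0.70 − 0.30) = 0.20 SD.

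**4. Scale.** The standard error of a 41 versus 24 contrast is √(1/41 + 1/24) = 0.257 SD. The largest screened bias in the table, 0.067 SD, is therefore about 0.067 / 0.257 = 26% of one standard error.

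**The case against.** Much of the opposing case stands and limits the point.

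- **Other safeguards.** A reader might infer that the screened regression is the only protection against confounding. It is not: the article matches on training length and commits to a difference-in-difference analysis. That analysis names no covariates, however, and would not by itself remove changes in supervision or case mix that differ between the cohorts. The statement on exploring confounders names none and does not commit to adjusting for them.
- **Unit of analysis.** Primary end points are collected per case, and Gartland class and consultant presence are case-level. The 36% and 52% do not apply to them. A case-level fit would have more observations, clustered within trainees, and the article gives no case numbers.
- **Size.** The screen alone did little harm in the simulations: small bias, and false positives of 5.1% to 5.2%.
- **Model.** The simulated cohort contrast is not the model in the article, which lists no cohort term. The bias figures are illustrative for that reason. The same gap means that the exposure itself is subject to the screen.
- **Separate adjustment sets.** A reader might infer that each end point gets its own covariates. The wording also allows significance on any one end point to admit a variable to all the models, so this is an ambiguity and not a stated defect.
- **Consultant presence.** It is recorded after training starts and may partly follow trainee skill. Forcing it into every model could remove part of a real simulator effect.
- **Pilot, condensed article.** This is true, but the candidate list and the entry rule are stated outright and not deferred to another document.

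**Conclusion.** The point holds in limited form. The article fixes a five-variable candidate list and a P<.05 entry rule. The rule can drop plausible trainee-level confounders by chance, can drop the exposure, and leaves consultant or assistant presence and patient age out although both are collected. At 65 trainees, with one value per trainee, a variable correlated 0.20 (0.25) with outcome passes about 36% (52%) of the time.

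On size, a stronger reading would be that the adjusted results will be seriously biased. The documents do not support it. They give no confounder strengths, no cohort imbalances and no direction, and they speak of potential confounders, not established ones. Under the assumptions shown, screening leaves 0.01 to 0.07 SD and complete ineligibility leaves 0.06 to 0.32 SD. The omission of plausible variables is thus the larger risk, but only if they differ between the cohorts. The plan should be changed because the rule is a poor one and cheap to replace.

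**What to change.** 1. Delete the P<.05 entry rule.
2. Keep cohort, or simulator exposure, in every primary end point model whatever its P value.
3. Pre-specify on subject-matter grounds one adjustment set common to the primary end point models: at least Gartland type, patient age and, where logbooks supply it for both cohorts, the number of prior SCHF procedures. The article does not describe how that count is obtained for comparators, so its availability needs checking. State in advance whether spatial awareness scores and procedures during follow-up belong in the set, noting that the latter accrue after exposure begins.
4. Report the estimates with and without consultant or assistant presence.
5. Report complications, which the article expects to be infrequent, descriptively or with minimal adjustment.

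The cost is a wording change in the analysis section, a few degrees of freedom and one extra sensitivity analysis. Gartland type, patient age and consultant or assistant presence are already on the data collection list.

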### Software

All analyses will be performed using the statistical analysis software R (R Foundation) [25].

### Data Management

Adverse events are unexpected with the use of the simulator, as trainees have operative experience and there is a low infection risk. Nevertheless, an independent data monitoring committee (DMC) has been setup consisting of 2 clinicians and will be reported to by a study researcher. Any adverse events will be reported immediately to the committee by trainees directly, and the committee may request an interim analysis of the data collected up to that point. The committee can request that the study be paused or discontinued based on the data they receive. The DMC will meet every 6 months to discuss this project.

Study researchers will ensure that the participants’ anonymity is maintained. The participants will be identified only by a participant’s ID number. Individual patients will not be contacted by a researcher. Identifiable patient and participant data will be anonymized and stored on secure University of Otago servers, and will only be accessible by the researchers directly involved with this data collection. Analysis will be performed only on anonymized data sets with an anonymous identifier instead of NHI numbers. The study will comply with the Data Protection Act, which requires all data to be anonymized as soon as it is practical to do so. Data will be stored for 10 years after the conclusion of the study and subsequently destroyed.

